## Abstract

**Background:**

Shoulder disorders are a common health problem in western societies. Several treatment protocols have been developed for the clinical management of persons with shoulder pain. However available evidence does not support any protocol as being superior over others. Systematic reviews provide some evidence that certain physical therapy interventions (i.e. supervised exercises and mobilisation) are effective in particular shoulder disorders (i.e. rotator cuff disorders, mixed shoulder disorders and adhesive capsulitis), but there is an ongoing need for high quality trials of physical therapy interventions. Usually, physical therapy consists of active exercises intended to strengthen the shoulder muscles as stabilizers of the glenohumeral joint or perform mobilisations to improve restricted mobility of the glenohumeral or adjacent joints (shoulder girdle). It is generally accepted that a-traumatic shoulder problems are the result of impingement of the subacromial structures, such as the bursa or rotator cuff tendons. Myofascial trigger points (MTrPs) in shoulder muscles may also lead to a complex of symptoms that are often seen in patients diagnosed with subacromial impingement or rotator cuff tendinopathy. Little is known about the treatment of MTrPs in patients with shoulder disorders.

The primary aim of this study is to investigate whether physical therapy modalities to inactivate MTrPs can reduce symptoms and improve shoulder function in daily activities in a population of chronic a-traumatic shoulder patients when compared to a wait-and-see strategy. In addition we investigate the recurrence rate during a one-year-follow-up period.

**Methods/Design:**

This paper presents the design for a randomized controlled trial to be conducted between September 2007 – September 2008, evaluating the effectiveness of a physical therapy treatment for non-traumatic shoulder complaints. One hundred subjects are included in this study. All subjects have unilateral shoulder pain for at least six months and are referred to a physical therapy practice specialized in musculoskeletal disorders of the neck-, shoulder-, and arm.

After the initial assessment patients are randomly assigned to either an intervention group or a control-group (wait and see). The primary outcome measure is the overall score of the Dutch language version of the DASH (Disabilities of Arm, Shoulder and Hand) questionnaire.

**Discussion:**

Since there is only little evidence for the efficacy of physical therapy interventions in certain shoulder disorders, there is a need for further research. We found only a few studies examining the efficacy of MTrP therapy for shoulder disorders. Therefore we will perform a randomised clinical trial of the effect of physical therapy interventions aimed to inactivate MTrPs, on pain and impairment in shoulder function in a population of chronic a-traumatic shoulder patients. We opted for an intervention strategy that best reflects daily practice. Manual high velocity thrust techniques and dry-needling are excluded. Because in most physical therapy interventions, blinding of the patient and the therapist is not possible, we will perform a randomised, controlled and observer-blinded study.

**Trial Registration:**

This randomized clinical trial is registered at current controlled trials ISRCTN75722066.

## Background

Shoulder pain is a common health problem in western societies. There are substantial differences in reported prevalence in the general population. The one-year prevalence of shoulder disorders has been reported to range from 20% to 50%. This wide range is strongly influenced for example by the definition of shoulder disorders, including or excluding limited motion, age, gender and anatomic area [1-3]. Of all shoulder patients who attend primary care physicians 50% recover within 6 months, meaning they do not seek any medical help after the first episode[1,4-6]. Chronicity and recurrence of symptoms are common [7,8]. According to the guidelines of the Dutch College of General Practioners [9], the recommended management of shoulder symptoms starts with educational information about the natural course of shoulder pain combined with the advise to avoid irritating and loading activities. The use of analgesics or NSAIDs is recommended for the first two weeks. When no recovery occurs within two weeks, subacromial or intra-articular injection therapy with corticosteroids are administered and eventually repeated. Finally, physical therapy is only recommended after a 6-week period when there are functional limitations (specifically an activating and time-contingent approach). International guidelines for shoulder pain, including the Clinical Guideline of Shoulder pain of the American Academy of Orthopaedic Surgeons [10] and the Shoulder Guideline of the New Zealand Guidelines Group[11] differ more or less from the Dutch guidelines in classification, recommended interventions and timeline, and order of interventions. Scientific evidence from randomized clinical trials, meta-analyses or systematic reviews for either the efficacy of multimodal rehabilitation, injection therapy, medication, surgery or physical therapy or the order of application of commonly used therapies is lacking [12-16].

An alternative approach to the management of persons with shoulder problems consists of a treatment aimed at inactivating MTrPs and eliminating factors that perpetuate them. MTrPs may be inactivated by manual techniques (such as compression on the trigger point or other massage techniques), cooling the skin with ethyl chloride spray or with ice-cubes followed by stretching of the involved muscle, trigger point needling using an acupuncture needle, or injection with local anaesthetics or Botulinum toxin, followed by ergonomic advises, active exercises, postural correction, and relaxation (with or without biofeedback)[17,18]. Over the years, MTrPs are increasingly accepted in the medical literature. Clinical, histological, biochemical and electrophysiological research has provided biological plausibility for the existence of MTrPs [19-24].

MTrPs are defined as exquisitely tender spots in discrete taut bands of hardened muscle that produce symptoms [25,26]. A previous study showed that MTrPs can be detected reliably by trained physiotherapists [27]. Palpation is still the only reliable method to diagnose myofascial pain clinically. In reviews addressing the efficacy of interventions in shoulder patients, MTrP therapy and myofascial pain are rarely mentioned [15]. However, some published case studies suggest that treatment of MTrPs in shoulder patients may be beneficial [28-31].

The primary aim of this study is to investigate the effectiveness of inactivation of MTrPs in shoulder muscles by physical therapy on symptoms and functioning of the shoulder in daily activities in a population of chronic a-traumatic shoulder patients when compared to a wait-and-see strategy. In addition, we investigate the recurrence rate during a one-year-follow-up period.

## Methods/Design

An examiner-blinded randomized controlled trial will be conducted, which has been approved by the ethics committee of the Radboud University Nijmegen Medical Centre, the Netherlands [CMO 2007/022].

### Participants/Study sample

Between September 2007 and September 2008, all consecutive patients referred to a physical therapy practice specialized in the treatment of individuals with musculoskeletal disorders of the neck, shoulder and arm are potential study participants. The referring physicians include general practioners, orthopaedic surgeons, neurologists and physiatrists. Patients are eligible if they have unilateral shoulder complaints (described as pain felt in the shoulder or upper arm) for at least six months. The patients present with persistent shoulder pain that has not spontaneously recovered. The patients are between 18 and 65 years old. Because the questionnaires are in the Dutch language, subjects must understand written and verbal Dutch. Patients who have been diagnosed (prior to the referral) with shoulder instability, shoulder fractures, systemic diseases (such as rheumatoid arthritis, Reiter's syndrome, diabetes), or who's medical history or examination suggests neurological diseases, or other severe medical or psychiatric disorders will be excluded from the study. The project leader will check all the available information from referral letters, additional information from the general practitioner and from the patients. All eligible patients will be informed of the study and will be invited to participate. Patients who are willing to participate will be asked to review and sign the written informed consent.

### Measurements

Before randomization, all participants will be assessed during an individual baseline test session. They will complete a battery of questionnaires and tests, determining data on social, demographic, and physical factors, and baseline values for the outcome measures. In addition, subjects will complete the DASH, RAND-36-dutch language version, and passive range of motion tests of the shoulder (PROM). During the initial assessment, MTrPs will be identified, based on compression-produced pain that is recognized by patients as their own shoulder pain. If no MTrPs are detected, the subjects will be excluded from the study. All measurements will be performed by the same independent observer, who is not employed by the physical therapy practice (This is to create optimal blinding of the observer, who is now not able to recognise the subjects). The observer is trained in identifying MTrPs and has several years of clinical experience in MTrP therapy. The observer participated in a former reliability study of MTrP palpation. The baseline measurements will be at T0, the second measurement (T1) will be 6 weeks after the first assessment session, the third (T2) will be 12 weeks after the first assessment session. All measurements [see box 1] will be performed outside the physical therapy practice to assure that the observer will not recognise any of the study participants when they come to the physical therapy practice for their treatment. After this first assessment, the patients will be randomly assigned to one of two groups: the intervention group or the control group. The patients in the control group will stay on the waiting list and will not receive any treatment. They are allowed to use over-the-counter painkillers during this 12-week period. After 6 weeks and 12 weeks, respectively, they will be examined by the same blinded observer. After 12 weeks they will receive the same physical therapy program as the experimental group [see Figure 1]. The initial trial ends after 12 weeks, but 6 months and 12 months after the start of the experimental intervention shoulder function of the subjects will be re-evaluated with the DASH-Dutch language version.

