### Control of intervention integrity

To enhance the integrity of this complex intervention, every week all participating physical therapists will discuss the content of each therapy session with the researcher (CB) without mentioning names or other information which will assure the blinding of the independent researcher (CB). After 6 and 12 weeks, the patients of the intervention group will interviewed about the content of the received treatment sessions to assure that all patients will be treated according to the protocol. If patients are not treated according to the protocol, they will be identified and participation may be discontinued.

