◦ For the measurement of internal rotation the patient is in a prone position. The shoulder is 90° abduction, and the forearm is in neutral position. This position is defined as the position of 0°. The observer than performs internal rotation until pain limits the range of motion or the extreme of the range is reached. The sensor is placed against the volar side of the forearm. The normal range of motion is 70°

◦ For the measurement of horizontal adduction the patient is in a supine position. The arm is in 90° abduction. This position is defined as the position of 0°. The observer performs adduction, while the arm stays in the vertical plane, until pain limits the range of motion or the extreme of the range is reached. The normal range of motion is 135°

• Finally the total number of treatment sessions will be counted. This is done by an assistant, who is not involved in the study by using the administration-software of the practice [see Table 1].

**Table 1 T1:** Overview of variables

**Variable**	**T0 Baseline**	**T1 After 6 wk**	**T2 After 12 wk**	**Measured by**
***Age****	X			Interview
***Gender****	X			Interview
***Work***	X			Interview
***Dominant side affected***	X			Interview
***Duration of the complaints****	X			Interview
***DASH ***DLV	X	X	X	Questionnaire
Use of ***medication***	X	X	X	Interview
Use of ***other therapy***	X	X	X	Interview
***Work ***%	X	X	X	Interview
***Improvement ***(percentage of perceived improvement)		X	X	Interview
***Number of involved muscles***	X	X	X	Assessment
***No. of treatment sessions***			X	Assessment
***Health status ***for baseline comparison	X			RAND-36 DLV
***Existence and severity of symptoms of depression***	X			Beck Depression Inventory
***Shoulder Passive ROM***	X	X	X	Goniometry
• flexion	X	X	X	
• abduction	X	X	X	
• external rotation	X	X	X	
• internal rotation	X	X	X	
• cross body adduction	X	X	X	

*Age, gender and duration of the complaints seem to be important prognostic variables [53].

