### Blinding

Blinding of the patients or the physical therapists, who are involved in the treatment, is impossible due to the treatment characteristics.

An independent observer will collect baseline data and outcome data. The independent observer is blinded. The successfulness of the blinding procedure will be evaluated by asking the observer to which group she believes the subjects belong.

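### As written, the blinded observer appears also to interview patients at weeks 6 and 12, which puts the blinding of the trigger-point count and passive range of motion at risk

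*Protocol article*

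**What the plan says.** The Abstract presents observer blinding as the answer to the impossibility of blinding patients and therapists: "we will perform a randomised, controlled and observer-blinded study". The Measurements section gives the work to one person: "All measurements will be performed by the same independent observer, who is not employed by the physical therapy practice". It adds, for the control group, "After 6 weeks and 12 weeks, respectively, they will be examined by the same blinded observer". The Blinding section agrees: "An independent observer will collect baseline data and outcome data. The independent observer is blinded".

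Table 1 lists what is collected and by what mode. Medication use, use of other therapy and work percentage are obtained by interview at T0, T1 (6 weeks) and T2 (12 weeks). The "percentage of perceived improvement" is obtained by interview at T1 and T2. The table does not name the interviewer.

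The section Control of intervention integrity describes a further conversation, also after 6 and 12 weeks, in which "the patients of the intervention group will interviewed about the content of the received treatment sessions". No interviewer is named there either.

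**The concern.** Patients know whether they are being treated or are on the waiting list. If the person who palpates for trigger points and measures range of motion also asks them about therapy and improvement, some will reveal their group without meaning to.

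The examiner-rated outcomes are open to expectation. A trigger point counts when the patient recognises the pain that compression produces. Passive movement is stopped when pain limits it or, for abduction, when the examiner feels the scapula begin to rotate. An examiner who knows the group can influence how hard she presses and where she stops. The stake is detection bias in these secondary outcomes, in the one part of the trial where blinding was feasible.

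**Working it through.** No figure in the plan depends on this point: blinding does not enter the sample-size calculation. The check is a comparison of sections.

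1. **Who interviews?** Measurements assigns all measurements to the observer, and Blinding assigns her baseline and outcome data. Much of the baseline data in Table 1 (age, gender, work, duration of complaints) is itself obtained by interview, so interviewing falls within her stated task at T0. Where another person collects an item, the article says so: an assistant takes the number of treatment sessions from the practice software. No such exception is made for the T1 and T2 interviews. The natural reading is that the observer holds them. This is an inference, because no sentence states it.

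2. **Can the interviews reveal the group?** The Blinding section says patients cannot be blinded, and Measurements says controls receive no treatment for 12 weeks. Questions about therapy used and improvement felt invite remarks about still waiting or about the sessions. They do not force disclosure.

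3. **Do the stated safeguards prevent it?** There are three.
   - An observer from outside the practice: stops her recognising patients who come for treatment.
   - Measurement away from the practice: serves the same purpose.
   - The observer's group guess: may detect unblinding, but cannot prevent it.

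   None of them governs what a patient says during the visit. The article states neither an order of examination and questions nor an instruction to patients not to disclose.

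4. **What is exposed?** One trigger-point muscle count plus five movements (flexion, abduction, external rotation, internal rotation, cross-body adduction) makes 1 + 5 = 6 outcomes. Two follow-up visits give 6 × 2 = 12 between-group comparisons, which is an upper limit. If the physical tests always came before the questions, T1 would be protected from that day's interview. The same observer sees the patient again at T2, so something learned at the T1 interview could still affect the 6 comparisons at T2. Visit order alone is therefore not enough.

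5. **What is not exposed?** The DASH is a self-report questionnaire completed by patients who know their group. Its risk of bias is the same whether or not the observer stays blinded.

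**The case against.** The strongest reply is that the interviewer is never named. Table 1 gives modes of collection, not persons. The statement about all measurements refers to a box that is not in the text available, and the Secondary outcomes section gives the independent examiner only the physical tests. Since an assistant counts the sessions, all measurements cannot mean every row of Table 1. This stands as a limit on certainty. It does not displace the plain reading, because the Blinding section gives the observer outcome data without exception.

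Second, a reader might infer that the plan itself defeats the blinding. The documents do not support that. Use of other therapy is also asked before randomisation, so it reads as care outside the trial. Controls may take over-the-counter painkillers, so medication does not identify a group. A work percentage or an improvement percentage does not either. Disclosure is a risk, not a certainty.

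Third, a reader might infer that the observer holds the treatment-content interview, which would reveal the group outright because only intervention patients have it. Nothing says that she does. The same section keeps names out of the weekly discussions with therapists in order to protect blinding, so the issue was in view. A condensed article may leave the interviewer to the full protocol. It is worth settling in the same edit, but it is not evidence of a failure.

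Fourth, a reader might extend the concern to the primary outcome. The article already calls the DASH self-report and says patients cannot be blinded. It does not claim that observer blinding protects the DASH.

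**Conclusion.** The point holds as a risk to blinding. On the natural reading of Measurements, Blinding and Table 1 together, one blinded observer questions unblinded patients at T1 and T2 and also rates the trigger-point count and passive range of motion. The stated safeguards do not prevent disclosure in the room.

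At most 12 secondary comparisons are exposed. That ceiling would be reached only if the group became known before every examination, which the document does not show. The size of any bias cannot be estimated from the document. The primary analysis and the sample size are unaffected.

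The conclusion rests on one assumption: that the observer takes the interviews. If the full protocol names someone else and keeps the answers from the observer, the point is met and only the wording of the article needs changing. The change is worth making because it costs almost nothing and protects outcomes that depend on judgement.

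**What to change.** At T1 and T2:

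- Complete the trigger-point count and range-of-motion tests before any questions are asked.
- Instruct patients beforehand not to disclose their group to the observer.
- Record the observer's group guess directly after the physical tests, so that it reflects what she knew while rating.
- Collect other therapy, medication, work percentage and perceived improvement on a self-completed form that the observer does not see, at either visit.
- State that the treatment-content interview is held after the assessment by someone other than the observer, and not by the assistant who generates the allocation. Keep that assistant out of the self-completed forms as well: the Randomization section describes the role as otherwise uninvolved, and it should stay so.

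The cost is one short form, a fixed visit order and a named interviewer. The downside is a few more blank items than an interview would give. Sample size, treatment and the choice of outcomes do not change.

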**Figure 1 F1:**
[figure not shown]
recruitment and experimental plan.

### Intervention

The patients in the intervention group will be treated by a physical therapist once a week for a maximum period of 12 weeks. All participating physiotherapists are experienced in treating patients with long-lasting shoulder symptoms and patients with MTrPs and myofascial pain, especially in the upper part of the body. They are trained and skilled in the identification of MTrPs and received a certification in manual trigger point therapy. The treatment starts with inactivation of the active (pain producing) MTrPs by using manual techniques (compression on the trigger point, manual stretching of the trigger point area and the taut band) combined with "intermittent cold application by using ice-cubes followed by stretching the muscle" according to Travell [32] to further inactivate the MTrPs. Manual pressure will decrease the sensitivity of the painful nodule in the muscle while other massage technique will mobilize and stretch the contracted muscle fibres. The application of the ice-cubes has a desensitizing effect, and makes it easier to stretch shoulder muscles. Each treatment session will end with a heat application to increase the circulation of the involved muscles.

Patients will be advised to do stretching exercises and will be taught to perform these correctly by means of surface-electromyography-assisted stretching[33,34]. Furthermore they will be advised to perform relaxation exercises, and to applyheat (like a hot shower, hot packs) several times (at least twice) a day. If there is abnormal measurable higher electromyographic activity in the upper trapezius muscle (measured by surface Electromyography (sEMG) using a Myomed 932 [Enraf Nonius, Delft, the Netherlands]) during standing and/or sitting [35], relaxation exercises will be performed using a portable myofeedback device (Myotrac I, Thought Technology, Quebec, Canada). Abnormal sEMG activity is defined as a constantly measured value above 1%–5% of the maximally voluntary contraction [36-39], which is in general above 10 microvolt, during several minutes and the patient is not able to relax the muscle spontaneously or on request. Finally, all patients will receive ergonomic recommendations, andinstructions to assume and maintain "good" posture [40,41]. Manual high velocity thrust techniques of the cervical spine and the shoulder and dry needling are excluded from the treatment protocol, because not all participating physical therapists are skilled to perform these techniques. The content of each session may vary as it depends on the findings during the first treatment session and the results of the previous treatment sessions. Thus, there are differences in the content of the individual treatments, but within the limits of the treatment protocol.

